### Data collection procedures

Baseline: Following enrollment, we will collect baseline data from the patient, parent or caregiver, and ED clinician. This will include contact information, demographic details, medical history, and relevant clinical variables. Accounting for pre-injury functioning is essential to identify preexisting mental and behavioral health symptoms and to distinguish them from new or worsening symptoms following injury -- a standard practice in post-injury assessment [22, 54]. Therefore, we will gather baseline mental health and related data reflecting the patient’s status prior to the mTBI. This will include the GAD-7, PHQ-8, PedsQL, social determinants of health, Rivermead, and mental health service utilization history (Table 1).

**Table 1 Tab1:** Schedule of evaluations

Construct	Measure	Respondent	Baseline	Acute Period	Outcome Period	
			ED ^a^	1 to 2 weeks ^a^	1-month ^a^	3-months ^a^
Eligibility	CRF	RC	x			
Contact information	CRF	Parent	x			
ED clinical variables	CRF	Physician	x			
Medical record variables ^b^	CRF	RC	x			
Family demographics and medical history	CRF	Parent	x			
Anxiety	GAD-7 ^d^	Child	x		x	x
Depression	PHQ-8 ^d^	Child	x		x	x
Health related quality of life	PedsQL^d^	Child and Parent	x		x	x
Behavioral screening	SDQ ^d^	Parent	x		x	x
mTBI symptoms	Rivermead ^d^	Child	x ^c^	x^c^	x^c^	x^c^
Mental health utilization	Questionnaire ^d^	Parent	x	x	x	x
Early physical activity/Return to school	Questionnaire ^d^	Child		x		

*Abbreviations*: *CRF *Case review form, *GAD-7* Generalized Anxiety Disorder-7, *PHQ*-*8 *Patient Health Questionnaire-8, *SDQ *Strength and Difficulties Questionnaire, *Rivermead *Rivermead Post Concussion Symptom Questionnaire

^a^Collected via automated digital surveys or the Central Outcomes Center at the Kennedy Krieger Institute

^b^﻿RC completion of medical record variables will be completed after hospital discharge

^c^Current symptoms rated compared to pre-injury baseline symptoms

^d^Time to completion (in minutes): GAD-7 (2), PHQ-8 (2), Rivermead (5), PedsQL (5), SDQ (5), Mental health utilization (1), Early physical activity/return to school (1)

Follow up: Automated digital surveys will be sent to the parent or caregiver for the acute period (1 to 2 weeks after the index ED visit), 1-month follow-up, and 3-month follow-up. The Central Outcomes Center at the Kennedy Krieger Institute will monitor survey completion and if necessary, will contact parents or caregivers to complete the follow up surveys. After completion of each baseline and follow up survey, patients and parents or caregivers will be emailed a gift card of their selection using the Tango gift card service. In cases where the parent or caregiver does not have an email address, the Central Outcomes Center will mail gift cards to the home address of the patient and parent or caregiver.

### Analysis

We will select candidate variables a priori based on prior studies and clinical expertise. Variables will include patient demographics, injury characteristics, pre-injury mental health diagnoses, treatment, early physical activity, and persistent mTBI symptoms (at 1 to 2 weeks). We will elicit clinical expertise during the coding of the clinical prediction steps, including rules for addressing item-level nonresponse. We will evaluate the impact of individual predictors by estimating odds ratios with 95% confidence intervals.

We will rely primarily on Classification and Regression Tree (CART) analyses using binary recursive partition in addition to multivariable logistic regression for model development. For the derivation cohort, feature selection will separately use both elastic net regularization and bootstrapped backward elimination models, with selections compared to determine the model specification for estimating model parameters. We will derive a low-risk component of the risk stratification model using binary recursive partitioning. Recursive partitioning allows for the inclusion of patients with missing predictors by substituting “surrogate” variables that partition patients as the missing variables would. Therefore, patients with missing observations for one or more predictors are not necessarily dropped from the analysis (as they often are in logistic regression analysis). While this property is attractive, it may also lead to bias if there is excessive use of surrogate variables. Therefore, if more than 20% of the data are missing for any variable (consistently across all sites), that variable will be excluded from consideration into the model. This proposed restriction is also important from a practical standpoint, because if a frequently missing variable were part of the prediction rule, the clinician would be unclear about what to do with patients missing this information. We will monitor missingness throughout the study to allow for training of study personnel, if necessary and appropriate. In the construction of the decision tree, we will assign misclassification “costs” to specific misclassification errors. We will also enter sites into the analysis to explore whether any site exerts disproportionate influence in the generation of the model.

To complement the low-risk component of the risk stratification model created by recursive partitioning, we will use the same candidate variables to conduct multivariable logistic regression analyses to derive a risk score model for those patients identified as having greater than low risk (i.e. those who do not meet low-risk criteria). We will first conduct single variable logistic regression to identify all variables that have any association with the outcome.

Internal cross-validation methods will be used to refine the model. Following the development of the final model from the derivation cohort, we will use the Framingham Study method to translate logistic regression estimates into simple risk scores. Performance of the resulting risk-stratification models (original and simplified) will be validated in the validation cohort [55]. Model performance will include assessments of discrimination and calibration. Finally, we will also use random forests to derive a prediction algorithm for mental health sequelae. Many trees are independently grown using recursive partitioning on bootstrapped samples of observations. The predictor at each node in each tree is selected from a random subset of predictors and trees are grown without pruning.

Secondary outcomes will be analyzed using descriptive statistics to further characterize the study population. We will analyze how the primary risk model prediction is associated with secondary outcomes. For this analysis, we will use the combined derivation and validation cohorts.

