**Methods:**

We will conduct a multicenter prospective observational cohort study enrolling patients aged 11–17 years who present to the emergency department (ED) with mTBI within 3 days from injury. We will enroll consecutive patients into separate derivation and validation cohorts using different enrolling sites. Baseline data, including pre-injury mental health status, and clinical variables will be collected from patients, caregivers, and ED clinicians. We will collect validated measures during the acute period (1 to 2 weeks), 1-month, and 3-months post-injury including: the Generalized Anxiety Disorder-7 (GAD-7), Patient Health Questionnaire-8 (PHQ-8), Pediatric Quality of Life Inventory (PedsQL), Rivermead Post-Concussion Symptoms Questionnaire, and the Strengths and Difficulties Questionnaire (SDQ). Our primary outcome is a composite measure of clinically significant new or worsening in anxiety or depression at 1 or 3 months. Secondary outcomes include persistent post-concussive symptoms, reduced quality of life, and new behavioral or emotional difficulties. We will analyze associations between baseline factors and outcomes to derive and validate a clinical prediction tool.

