Early Physical Activity/Return to School Questionnaire: Early physical activity is defined as any level of physical activity, other than no activity, seven days after the index ED visit [12]. Return to physical activity within seven days of injury is associated with lower rates of post-concussive symptoms [12, 18]. We will assess for this early physical activity using a single self-report question categorized as no activity (e.g., physical rest), light to moderate aerobic activity (e.g., walking, swimming, stationary cycling, or jogging); heavy aerobic activity (e.g., running) or non-contact training drills (e.g., passing drills with teammates); and full-contact practice or games (e.g., normal training and return to competition).

Similarly, early return to school (defined as < 3 school days missed) is associated with lower post-concussive symptom burden at 14 days [53]. We will assess early return to school using a single self-report question 1 to 2 weeks after the index ED visit, categorized as early return to school or late return to school (3 or more school days missed) [53]. 

Mental Health Utilization Questionnaire: We will assess the patient’s mental and behavioral health treatment based on previously developed methodology, assessing parent-reported treatment and services used and unmet needs [24, 25]. This questionnaire is available in English and Spanish and takes less than two minutes to complete.

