## Discussion

Our prospective cohort study aims to evaluate the mental health sequelae of mTBI in children and adolescents, with a focus on identifying early predictors of post-injury anxiety and depression. While much of the pediatric mTBI literature has focused on persistent post-concussive symptoms such as headaches or dizziness, there is growing recognition of the frequency and importance of emotional and behavioral outcomes following mTBI. Our study addresses this gap by incorporating validated mental health assessments at multiple time points and by analyzing their relationships with baseline characteristics.

Although most children with mTBI recover within a few weeks, a substantial proportion experience persistent symptoms, including emotional and behavioral difficulties, that may affect their functioning and quality of life [56–60]. These include elevated rates of anxiety, depression, and post-concussive symptoms for months following injury, even among children without prior psychiatric diagnoses [8, 61, 62]. For example, Zemek et al. found that 30% of children had persistent post-concussion symptoms at 28 days, and emotional symptoms were among the most commonly reported [22]. Other longitudinal studies have demonstrated that early symptom burden—particularly emotional and cognitive symptoms—may predict longer-term mental health difficulties [63–65]. However, limitations of previous work include small or homogeneous samples, retrospective designs, and inconsistent use of validated tools to assess changes over time. Moreover, few studies have rigorously assessed pre-injury mental health status, making it difficult to distinguish new-onset symptoms from preexisting conditions. Our study addresses these gaps by prospectively tracking a diverse cohort, using validated measures, and systematically capturing pre-injury functioning to better interpret post-injury changes.

The primary outcome—a composite measure of clinically significant worsening in anxiety or depression using the GAD-7 and PHQ-8—will allow us to capture meaningful mental health changes in the months following injury. By anchoring this outcome to minimal clinically important differences, we aim to ensure clinical relevance and interpretability. In addition, the inclusion of secondary outcomes such as persistent mTBI symptoms, quality of life changes, and new behavioral challenges will provide a more comprehensive understanding of the broader impact of mTBI.

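### The tool is described as derived from baseline factors, but two candidate predictors are measured 1 to 2 weeks later and no time of prediction is fixed

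*Protocol article*

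**What the plan says.** **Description of the tool.** The Methods part of the abstract says: "We will analyze associations between baseline factors and outcomes to derive and validate a clinical prediction tool". The Discussion, speaking of the mental health assessments, says that the gap is addressed "by analyzing their relationships with baseline characteristics".

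**Meaning of baseline.** The section on data collection procedures says: "Following enrollment, we will collect baseline data from the patient, parent or caregiver, and ED clinician". Table 1 heads the baseline column ED and gives the acute period at 1 to 2 weeks a column of its own.

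**Candidate predictors.** The Analysis section names demographics, injury characteristics, pre-injury mental health diagnoses, treatment, "early physical activity, and persistent mTBI symptoms (at 1 to 2 weeks". For the risk score it adds that "we will use the same candidate variables to conduct multivariable logistic regression analyses".

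**Timing of the last two candidates.** Early physical activity is defined as "any level of physical activity, other than no activity, seven days after the index ED visit". Table 1 marks its questionnaire in the 1 to 2 week column only. Follow-up surveys start with the "acute period (1 to 2 weeks after the index ED visit".

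**Exclusion rule.** A variable with more than 20% missing data, consistently across sites, is not considered for the model. The practical reason given is that otherwise "the clinician would be unclear about what to do with patients missing this information".

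**Performance target.** The Sample size section sets a useful rule at an AUROC of at least 80%. It does not say at what time after injury that applies.

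**The concern.** The time of prediction decides which predictors are admissible and what a validated performance figure means. Here two descriptions of the inputs stand side by side. One is limited to what is known at the ED collection. The other also draws on information that comes into being a week or two later. The variable selection would settle which of the two tools the study delivers, because the plan does not.

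At stake is the interpretation of the main result. A reader of the abstract will take the reported discrimination, sensitivity and calibration as those of a baseline-factor tool. If an acute-period variable is in the final model, those figures belong to a later prediction, and the study would have nothing to report for the tool as the abstract describes it. Retention is plausible: the Discussion cites longitudinal work in which early symptom burden may predict later mental health difficulties, and the questionnaire section links early activity to fewer post-concussive symptoms.

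**Working it through.** The point rests on comparing sections, not on arithmetic.

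1. **The plan's own figures.** Derivation: 1,400 × 0.25 = 350 events, and 350 / 35 = 10 events per predictor degree of freedom. Validation: 1,080 × 0.25 = 270 events. For a sensitivity of 0.90, the Wald half-width is 1.96 × √(0.90 × 0.10 / 270) = 0.0358, or 3.6%. The exact interval is 0.8578 to 0.9331, half-width (0.9331 − 0.8578) / 2 = 0.0376, which matches the stated ±3.8%. These figures reproduce and do not bear on this point.

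2. **Candidates against time of measurement.**

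| Candidate group (Analysis) | When known | Source |
|---|---|---|
| Demographics, injury characteristics, pre-injury mental health diagnoses | Baseline (ED column; chart review after discharge) | Table 1 |
| Treatment | Not specified in the list | Analysis |
| Early physical activity | Refers to day 7; asked at 1 to 2 weeks | Validated questionnaires; Table 1 |
| Persistent mTBI symptoms | 1 to 2 weeks | Analysis; Table 1 |

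Two of the six named groups therefore lie outside the baseline column.

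3. **Reach within the tool.** The tree gives the low-risk component, and the logistic score covers children who are not low risk. Both draw on the same candidates. If the tree keeps an acute-period variable, the low-risk classification may have to wait for it. If only the score keeps one, the score must wait. In either case the whole tool is complete only at 1 to 2 weeks. Surrogate splits do not resolve this: they exist in the tree and not in the score, and the Analysis section itself warns against relying on them heavily.

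4. **Does the 20% rule settle the time of prediction?** No. It counts missing values in the study data. It does not ask whether a variable is available when the tool is used. A well-completed 1 to 2 week survey passes the rule however early the tool is meant to be applied.

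5. **Do the predictors overlap the outcome?** No. The primary outcome is assessed at 1 and 3 months, after the acute-period survey. The problem is the time of use, not leakage of the outcome into the predictors.

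6. **Can a loss of AUROC be derived?** No. It would need the share of predictive information carried by the acute-period variables and how far ED variables can replace it. The article gives neither. Table 1 also shows the symptom questionnaire at the ED collection, so a refitted baseline model could recover part of what is removed.

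**The case against.** The strongest reply is that nothing obliges the tool to work at the index visit. The stated aims are early identification and referral, help in managing adolescents with mTBI, and post-injury care pathways. The ED is where children are recruited. A tool completed 1 to 2 weeks after injury fits all of these aims, and a clinician at that time can simply ask about activity and symptoms. The abstract itself mentions the acute-period measures. The Discussion phrase about baseline characteristics concerns the mental health assessments and does not define the tool's inputs. The candidate list is a summary, and a fuller document may refine it.

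Most of this stands. A reader might infer that the rule would be unusable in the ED, that these variables are missing for every patient at the point of use, or that the tool has no single point of use. The first two inferences assume use in the ED, which the article never states. The third is wrong, because a tool that retains a 1 to 2 week variable has a clear point of use at 1 to 2 weeks. A reader might also infer that a baseline-only model must miss 0.80 by a calculable amount. The article has no figure to support that, and it does not tie the 0.80 criterion to a baseline tool.

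What the reply does not remove is the contradiction. If the tool is meant for 1 to 2 weeks, the abstract's sentence on baseline factors is wrong. If that sentence is right, the two later candidates do not belong in the pool. This is a conflict in the published text and not a detail left to an analysis plan.

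**Conclusion.** The concern holds in a limited form. The abstract and the Analysis section describe different sets of inputs, and no section fixes the time of prediction. The consequence is conditional: if an acute-period variable is selected and survives the 20% rule, the validated performance applies at 1 to 2 weeks and none is reported for a baseline-factor tool. If no such variable is retained, the tool is a baseline tool and the figures apply as described.

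No size is attached to any difference in AUROC. The stated sample sizes and precision are unaffected. This is an inexpensive improvement to the plan and not a flaw that invalidates the design.

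**What to change.** 1. State the intended time of prediction, and bring the abstract's description and the candidate list in the Analysis section into agreement.
2. Prespecify two models with the same methods and data: a baseline-only model, and a 1 to 2 week model that adds the acute-period variables.
3. Validate both in the validation cohort, and report discrimination, sensitivity and calibration for each.
4. Say which of the two the 0.80 AUROC criterion in the Sample size section applies to.

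Stating the time of prediction and correcting the conflicting sentence would by itself remove the contradiction. The second model goes further and delivers the tool that the abstract describes, whichever variables are selected.

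The cost is a second run of the same analysis, with no new visits, data or participants. The baseline-only figure may be less favourable. The change can still be prespecified: enrollment was ongoing at manuscript submission, analyses start after follow-up is complete, and the investigators stay blinded to the validation data until the tool is developed.

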### Sample size

We specified that a useful clinical prediction rule would have a true discriminatory capacity, as measured by the area under the receiver operating characteristic (AUROC) curve, of at least 80%. To account for the large number of candidate variables in model derivation, we used variance inflation factors based on chi-square non-centrality parameters to convert actual sample sizes into effective sample sizes. We conservatively assume that at least 25% of the enrolled patients will experience the primary outcome [7–10]. A derivation cohort of at least 1,400 patients would provide approximately 350 patients with mental health sequelae, allowing for more than 35 predictor degrees of freedom. The planned validation sample size of 1080 patients (accounting for loss to follow-up) provides adequate precision for estimates of discrimination performance. For example, at a threshold of 90% sensitivity, the 95% confidence interval for sensitivity will have a size of approximately ± 3.8%.

### Missing data

The primary and secondary outcomes will be collected at two time points (1- and 3-month follow-up) reducing the risk of loss to follow-up. Due to the multiple follow-up times, we anticipate low missingness rates for the primary and secondary analyses. Patients who withdraw from the study or are lost to follow-up will have all available data used in the analysis. If a substantial number of patients are withdrawn or lost to follow-up, we will review and compare baseline characteristics to patients not withdrawn or lost, to assess empirically if these patients differ from those remaining in the study. The primary and secondary regression analyses will use complete case analyses if no more than 5% of cases are dropped from the analysis due to missing predictor variable data.

If missing data results in dropping more than 5% of cases for validation purposes, we will use regression-based multiple imputation within a chained equations framework. We will use standard regression methods for missing primary and secondary outcomes to use in imputation models, using bootstrapped stepwise variable selection to select predictors. We will impute and analyze 10 datasets. We will increase that number if the efficiency of the imputed datasets is less than 0.99. Following standard multiple imputation steps, we will estimate parameters and corresponding covariance matrices separately for each imputation dataset and then pool the results.

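### The stepwise rule for outcome-imputation models does not protect the tool's own predictors, so validated performance can be biased slightly toward no effect

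*Protocol article*

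**What the plan says.** All of the relevant text is in the protocol article, mainly in Methods, Missing data.

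- **Complete cases.** The primary and secondary regressions "will use complete case analyses if no more than 5% of cases are dropped from the analysis due to missing predictor variable data".
- **Trigger and framework for imputation.** "If missing data results in dropping more than 5% of cases for validation purposes, we will use regression-based multiple imputation within a chained equations framework".
- **Choice of imputation predictors.** "We will use standard regression methods for missing primary and secondary outcomes to use in imputation models", and the sentence ends "using bootstrapped stepwise variable selection to select predictors".
- **Number of imputations.** "We will impute and analyze 10 datasets", with more if efficiency falls below 0.99.
- **Related rule in Analysis.** For predictors, "if more than 20% of the data are missing for any variable (consistently across all sites), that variable will be excluded".

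The article names no variable that must stay in an imputation model. It gives no selection threshold and no separate specification for models that impute missing predictors. Study design and setting says that the tool is finalised on the derivation cohort before it is tested in the validation cohort.

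**The concern.** An imputation model should contain every variable of the analysis that will use the imputed data. If a tool predictor is left out of the model for a missing outcome, the imputed outcomes carry no association with it beyond what the retained predictors convey. Scoring the tool against them then mixes observed outcomes, which follow the predictor, with imputed outcomes, which do not. Discrimination falls and the calibration slope drops below 1. Rubin-type pooling does not remove this, because all the imputed datasets share the same omission.

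Stepwise selection tends to drop weak predictors. The Background says that no single factor predicts strongly, so a tool built from several modest contributors is plausible. The Analysis section also relates the tool's predicted risk to the secondary outcomes in the combined cohorts. The selection sentence covers secondary outcomes too, so that association can be attenuated in the same way.

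At stake is a small downward error in the validated performance of a tool whose stated target is an AUROC of at least 0.80.

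**Working it through.** **1. The plan's own figures (Sample size).** The article gives no figure for imputation bias. The nearest is the precision of sensitivity.
- Validation events: 1,080 × 0.25 = 270.
- At 90% sensitivity, 243 of 270, the exact (Clopper-Pearson) interval is 85.8% to 93.3%, a half-width of 3.76%. This reproduces the stated ±3.8%. The plain Wald value is 1.96 × √(0.9 × 0.1 / 270) = 3.58%.

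**2. Yardstick for an AUROC loss.** Hanley-McNeil with A = 0.80, 270 events and 810 non-events:
- Q₁ = A/(2 − A) = 0.6667; Q₂ = 2A²/(1 + A) = 0.7111.
- Variance = [0.16 + 269 × (0.6667 − 0.64) + 809 × (0.7111 − 0.64)] / (270 × 810) ≈ 64.86 / 218,700 = 0.000297.
- SE ≈ 0.017; 95% half-width ≈ 0.034.

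**3. Missing outcomes, bootstrapped stepwise selection.** Taken from the article: n = 1,080, 25% prevalence, AUROC about 0.80, 10 imputations. Assumed: 10 independent normal predictors with log-OR 0.15 to 0.88; backward elimination at p < 0.05 in 20 bootstrap samples, keeping variables chosen in more than half; 60 runs.

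| Outcome-imputation model | AUROC, 10% missing | Slope | AUROC, 20% missing | Slope |
|---|---|---|---|---|
| Full data, nothing missing | 0.7963 | 0.994 | 0.7974 | 0.996 |
| All tool predictors forced in | 0.7949 | 0.986 | 0.7964 | 0.992 |
| Bootstrapped stepwise | 0.7941 | 0.981 | 0.7940 | 0.979 |
| All tool predictors omitted | 0.7667 | 0.840 | 0.7366 | 0.704 |

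- Stepwise against forced-in: 0.7949 − 0.7941 = 0.0008 and 0.7964 − 0.7940 = 0.0024, so about 0.001 to 0.002. The Monte Carlo standard errors of the differences from full data were 0.0006 to 0.0011, so the 10% result alone is close to simulation noise.
- Predictors with log-OR of about 0.39 or more were always kept. Those near 0.29 were kept in 85% to 93% of runs. Those at 0.15 to 0.20 were dropped in about 43% to 65%.
- For that weakest group, mean log-ORs were about 3% to 9% lower than with all predictors forced in (for example 0.90/0.93 = 0.97 and 1.02/1.12 = 0.91).

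**4. A less favourable scenario.** Assumed: n = 1,080, 20 weak predictors, single-sample backward elimination at p < 0.05, 200 runs. The AUROC was 0.766 with selection and 0.769 with all predictors at about 11% missing (loss 0.003), and 0.761 against 0.767 at about 25% missing (loss 0.006).

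**5. Size against the yardstick.** 0.001/0.034 ≈ 3%; 0.006/0.034 ≈ 18%.

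**6. Only if selection also governs models for missing predictors.** With the outcome omitted from the model for a missing predictor, that predictor's log-OR fell to about 0.89 to 0.92 of truth at 10% missing and 0.76 to 0.79 at 20%, the article's retention limit. A p < 0.05 rule kept the outcome in 100% of runs for the strongest predictor, in 88% to 93% at log-OR 0.29 and in 32% to 40% at 0.15. With the outcome forced in, the strongest predictor's log-OR was 1.00 to 1.01 of truth.

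**The case against.** The strongest reply has four parts.

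**Scope.** The selection sentence concerns models for missing outcomes. There the outcome is the variable being imputed, so it cannot be dropped. A reader might infer that the outcome is pruned from models for missing predictors. Chained equations do impute incomplete predictors, and the article specifies nothing else for them, but the sentence does not say that its rule extends there. A reader might also infer that the derivation odds ratios are biased. The trigger is worded "If missing data results in dropping more than 5% of cases for validation purposes", and the tool is fixed before validation, so the text does not establish this. Both limits stand.

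**Size.** The AUROC loss is well inside the sampling error of the validation cohort, and the article expects little missing data. This stands, and it sets the severity.

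**Weak predictors may not be in the tool.** Tool predictors must first survive elastic net and bootstrapped backward elimination, so the simulated mix may hold too many weak ones. This stands as a reason to treat the sizes as illustrative. It does not show that a predictor retained in derivation, with about 350 events, will be selected again among validation patients with observed outcomes.

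**Detail for the analysis plan.** A journal article need not list the variables forced into an imputation model, and the wording is compatible with selection among auxiliary variables only. The full plan, not shown, may already say so. But the article does state a selection rule, and read as written it protects no variable. That is enough for a request to clarify, not for a claim of serious error.

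**Conclusion.** The point holds as a minor one. As written, the rule can remove weak tool predictors from the models that impute missing outcomes, which can bias validated discrimination, calibration and the association of predicted risk with secondary outcomes slightly toward no effect. The simulated AUROC loss is about 0.001 to 0.006 with roughly 10% to 25% of outcomes missing. The effect on secondary outcomes was not simulated.

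These sizes rest on assumed effect sizes, independent predictors in the 10-predictor scenario, an assumed p < 0.05 threshold and imputation being triggered at all. A reader might infer that validation will be seriously understated, or that the 0.80 target is endangered. The documents do not support that: AUROC losses of about 0.03 to 0.06 (0.7963 − 0.7667 and 0.7974 − 0.7366) appeared only with all tool predictors omitted, and selection at this sample size reliably keeps the stronger ones.

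Attenuated odds ratios from dropping the outcome are a conditional concern. They arise only if the same selection is applied to models for missing predictors.

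**What to change.** Add one sentence to Missing data: every imputation model always contains all variables of the analysis it serves, meaning all tool predictors or the risk score in models for a missing outcome, and the outcome in any model for a missing predictor; bootstrapped stepwise selection is limited to auxiliary variables. The same sentence settles the ambiguity about models for missing predictors.

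The cost is that sentence and slightly larger imputation models. Enrollment was still under way when the article was submitted, and analysis starts only after follow-up ends (Study status), so the wording can be settled before results are known. If the full analysis plan already forces these variables in, aligning the article's description with it is enough.
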